## Introduction

Otitis media (OM) is a common childhood illness globally, with an estimated burden of more than 360 million episodes each year (1). OM is one of the primary reasons for presentations at healthcare facilities and for antibiotic prescriptions in children (2). There are varying disease pathologies, from episodic middle ear effusions to chronic drainage of purulent discharge through a perforation of the tympanic membrane. For most infants and children OM will resolve without treatment or intervention. However, some children are at high risk of more severe OM and long-term negative outcomes. Groups at higher risk for OM include children attending out of home childcare and Indigenous populations worldwide. Recognized risk factors for OM include age (with highest incidence between 6 and 11 months), exposure to tobacco and environmental smoke, reduced breast-feeding, and crowded living conditions (2).

Australia's Northern Territory (NT) faces some unique challenges. There is a vast geography with many widely dispersed small populations, with some residents living in very isolated areas. Multiple languages exist, and there is extensive population mobility linked to cultural and social traditions. Approximately 30% of the NT population are Aboriginal, compared to 3% Australia wide. Aboriginal people in the NT are generally younger, have lower educational attainment, have higher rates of chronic health problems, and live in more crowded housing than non-Aboriginal NT residents. 77% live in remote areas, contributing to difficulties in accessing health care and other services (3). The prevalence and severity of otitis media in these remote communities in northern and central Australia is extraordinarily high. Around 90% of children have some form of OM throughout their early years (including 15% with perforated tympanic membrane) (4–6).

All forms of OM are associated with hearing loss (7). The extreme prevalence of OM among Aboriginal children the NT makes this a significant public health problem. OM associated conductive hearing loss can impact the development of language skills and school preparedness when it occurs in children <4 years of age. However, there are limited audiology data for Aboriginal children in this age group (8, 9). The relationship between OM disease status, hearing loss, and language development in this age group are still being established.

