### Data Sources, Management, and Amalgamation

A core group of investigators has maintained the EHRP research, ensuring funding, standardized methods for ear assessments and microbiology, long-term consistency of data collection, including cleaning and storage.

Ears were assessed using (video) pneumatic otoscopy or (video) otoscopy and tympanometry. Minimal change to diagnostic categories were made over the life of the program. Management of diagnostic categories of OM were made according to relevant guidelines at the time of each the study. Specialist referrals (audiology and ENT) were also made according to appropriate guidelines. In addition to otitis media diagnoses, detailed ear observations were recorded including tympanic membrane color, translucency, mobility, position (retraction, neutral or degree of bulging), perforation size and position.

Medical records of consented participants were also reviewed to collect additional data. This included non-study related clinician-diagnosed otitis media, all antibiotic prescriptions likely to influence otitis media and pneumococcal immunization data. Health data not related to OM or antibiotic use were not extracted.

Research nurses conducted standardized interview questionnaires with parents or caregivers regarding recognized risk factors. These included breastfeeding, smoking, family history of otitis media, and household occupancy. Observable general health indicators (runny nose, cough, visible skin problems) and weight and height were also collected as part of some studies. Original study data were collected on hard copy standardized forms for entry into secure electronic data storage systems.

Microbiological analysis of NP and ear discharge (ED) swabs for respiratory pathogens of interest used WHO-recommended standardized specimen collection, transport, storage, culture, identification and serotyping methods (Quellung) (17, 18) and are described in detail in Supplementary Material. Antibiotic sensitivity of bacterial isolates included disc diffusion predominantly by Calibrated Dichotomous Susceptibility (CDS) (19) and some E-test MIC determination.

Almost all studies collected a core set of clinical assessments and microbiological specimens and used the same standardized methods and data storage systems.

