### Data Limitations

Whilst this resource represents a comprehensive collection, data for all described fields were not included in every study due to the variation in study designs. Original eligibility criteria for participants varied across the RCTs according to the condition (specific OM diagnosis) and outcomes of interest, such as intervention trials for treatment of acute OM or chronic suppurative OM. Data from these studies will be used when they meet inclusion criteria for each research question. Inclusion and exclusion criteria for unpublished data studies can be accessed upon reasonable request. This dataset only includes research and health service data where individual consent was provided. Currently community-level data relating to other factors that may impact OM and NP carriage, including government initiatives such as swimming pools, housing, trends in primary healthcare services and policy, or widespread antibiotic use or mass drug administration for trachoma are not included in BIGDATA. These data could potentially be linked in the future.

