#### Aims

To describe prevalence of OM and severe OM over time and explore factors associated with these outcomes.

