#### Outcomes

Presence of OM and different OM diagnoses (proportions with 95% CIs) will be reported, per time period and region. Markers of severity (size of perforation, volume of discharge, bilateral disease) will be compared over time and vaccine eras. Regression analyses, corrected for repeated measures in the same participants where relevant, will be used to describe OM associations with modifiable risk factors, age, time, prior antibiotic use, gender and geographic region.

Multilevel mixed effects models will be used, utilizing fixed effects for antibiotics, vaccination, age, gender and year; and random effects for region.

(ii) Impact of increasing valency PCVs (PCV7, PCV10 and PCV13) on nasopharyngeal carriage dynamics of pneumococcal serotypes, and associated antibiotic resistance, and by region and other known predictors (risk factors).

PCV impact on nasopharyngeal carriage has been addressed in specific EHRP study publications, as the vaccines have been introduced (Table 1). However, a comprehensive descriptive analysis including all study data from the non-vaccine studies and pre-vaccine era has not been undertaken.

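### The OM model enters prior antibiotic use beside vaccination with no term for earlier OM, so the antibiotic coefficient is confounded by indication and the adjusted vaccination coefficient is not the total effect

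*Protocol article*

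**What the plan says.** Under question (i) of Research Questions and Hypotheses, the aim is "To describe prevalence of OM and severe OM over time and explore factors associated with these outcomes". The Outcomes paragraph says that regression analyses, corrected for repeated measures where relevant, will "describe OM associations with modifiable risk factors, age, time, prior antibiotic use, gender and geographic region". It then gives the model: multilevel mixed effects, "utilizing fixed effects for antibiotics, vaccination, age, gender and year; and random effects for region". Earlier OM is not among the terms.

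Three statements elsewhere in the article bear on how the antibiotic variable arises:

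- Introduction: "OM is one of the primary reasons for presentations at healthcare facilities and for antibiotic prescriptions in children".
- Data Sources, Management, and Amalgamation, on medical-record review: the data collected include "non-study related clinician-diagnosed otitis media, all antibiotic prescriptions likely to influence otitis media and pneumococcal immunization data".
- Same section, on study visits: "Management of diagnostic categories of OM were made according to relevant guidelines at the time of each the study".

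Question (ii) uses the same regression approach for pneumococcal carriage but is limited to non-interventional data. Question (i) states no such limit.

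**The concern.** Children receive antibiotics largely because they have OM, and a child with OM before is more likely to have it again. Prior antibiotic use then marks prior OM. A model that contains the first and not the second credits to antibiotics some of the risk that belongs to the child's disease history. The correction for repeated measures does not deal with this: it addresses correlation between visits of one child, and the only random effect stated is for region.

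The same term affects the vaccination coefficient. If vaccination prevents OM episodes, it also prevents prescriptions, so later antibiotic use is partly a consequence of vaccination. Holding it fixed changes what the vaccination coefficient estimates.

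At stake is the reading of two results that the Highlights promise to deliver: which factors raise or lower OM risk, and what the vaccines did. A neutral or protective antibiotic effect could be tabulated as a risk factor, and a vaccination coefficient that is not the total effect could be taken for it.

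**Working it through.** The article gives no effect size, prevalence of antibiotic use or strength of indication on this point, so there is no figure to reproduce. Every input below is an assumption. The results show direction and possible range, not an estimate for this dataset.

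**Hand check, true antibiotic effect null.** Assume 30% of children are OM-prone with 90% OM and 70% are not, with 50% OM. Antibiotics have no effect within either group. Let prior antibiotic use be 70% in the prone group and 30% in the other.

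- Antibiotic users: 0.3×0.7 + 0.7×0.3 = 0.21 + 0.21 = 0.42.
- P(OM | antibiotic) = (0.21×0.9 + 0.21×0.5)/0.42 = 0.294/0.42 = 0.700.
- P(OM | none) = (0.09×0.9 + 0.49×0.5)/0.58 = 0.326/0.58 = 0.562.
- OR = (0.700/0.300)/(0.562/0.438) = 1.82.

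With 60% against 40%, OR = (0.302/0.158)/(0.318/0.222) = 1.33. With 80% against 30%, OR = (0.321/0.129)/(0.299/0.251) = 2.09.

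These strata imply 0.3×0.9 + 0.7×0.5 = 62% OM overall, below the figure of around 90% in the Introduction, so a wider range was tried.

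**Simulation, 400,000 children per scenario.** Assumed inputs:

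- vaccine OR 0.70 on both prior and current OM;
- latent OM susceptibility with SD 0, 1 or 2;
- additional log-OR of prior OM on current OM of 0 or 1;
- P(antibiotic) 0.4 or 0.8 after prior OM, 0.1 otherwise;
- true antibiotic OR 1.0, 0.7 or 0.4;
- baseline OM about 50% or 88%.

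This makes 72 scenarios. In 60 of them earlier OM predicts current OM. Three logistic models were fitted: vaccine only; vaccine and antibiotic, as the article pairs them; and both plus prior OM.

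The antibiotic OR was:

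| True OR | Without prior OM (60 scenarios) | With prior OM added (all 72) |
|---|---|---|
| 1.0 | 1.20 to 5.05 | 0.99 to 1.02 |
| 0.7 | 0.87 to 4.09 | 0.69 to 0.79 |
| 0.4 | 0.50 to 2.85 | 0.40 to 0.53 |

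All 60 fitted values lie above the true value. They are not all above 1: 3 of 20 stay below 1 when the truth is 0.7, and 11 of 20 when it is 0.4. At the 88% baseline alone, a true 1.0 appears as 1.20 to 4.88. The gap left after adding prior OM reflects non-collapsibility of the odds ratio over latent susceptibility.

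Two conditions remove the bias. Where earlier OM does not predict current OM, a true 1.0 is fitted as 0.99 to 1.00. Where antibiotics are randomized, a true 1.0 is fitted as 1.00.

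**Vaccination coefficient.** The change is 1 − (log-OR with antibiotic)/(log-OR without). Across the 60 scenarios it ran from 14.5% attenuation to about 6% strengthening, with strengthening in 14. Where earlier and current OM were uncorrelated and antibiotics protective, strengthening reached 24%. Attenuation was usual where antibiotics mainly marked earlier OM. Strengthening arose where they truly protected, because vaccinated children then had less of that protection. Without the antibiotic term, the vaccine OR was its total effect, 0.65 to 0.82.

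**The case against.** The strongest reply is that question (i) is descriptive. Its aim and its Outcomes paragraph speak of associations, and nothing there says that the antibiotic coefficient will be read as an effect. The word impact heads questions (ii) and (iii), whose outcome is carriage, and the mechanism here is specific to OM outcomes. This stands in part. It limits the point to OM models and makes it largely one of interpretation. It does not remove it, because the Highlights say that the planned analyses will describe what increases or decreases OM risk.

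A second reply is that the model sentence is a summary. It omits the modifiable risk factors named just before it, so a fuller plan may define more covariates and the window for prior use. That is fair for the window, which is not raised here. The pairing of antibiotics and vaccination in one model is, however, stated.

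Third, some antibiotic exposure was randomized. Data Limitations refers to studies "such as intervention trials for treatment of acute OM or chronic suppurative OM", and these can enter question (i) when they meet its criteria. The bias does not apply to that exposure.

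Fourth, earlier OM may be a weak covariate. The article leaves out variables not collected in several studies or inconsistently defined, and says that fields vary by study. Where most children have had OM, a yes/no history varies little. This stands: adjustment will be incomplete.

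A reader might also infer that part of the vaccination effect is bound to be adjusted away. The documents do not support that. The difference can go either way, and changes in prescribing over the years may themselves confound comparisons between vaccine eras, which is a reason to show the antibiotic-adjusted estimate too.

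**Conclusion.** The point holds for OM outcomes and for antibiotic exposure that was not randomized. On the article's own account of why antibiotics are prescribed, the coefficient for prior use in the stated model is confounded by indication and shifted upward, provided earlier OM predicts current OM. How far cannot be estimated from the documents: the odds ratios of 1.33 to 2.09 and 1.20 to 5.05 under a true null rest wholly on assumed inputs. It would go too far to say that antibiotics will appear harmful, since a protective effect may merely look weaker.

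The antibiotic-adjusted vaccination coefficient is not the total effect if antibiotics follow vaccination. The direction of the difference is undetermined and its size was modest under the inputs tried: about 15% attenuation to 6% strengthening where earlier OM predicts current OM, and up to 24% strengthening otherwise.

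**What to change.** For OM outcomes, report the vaccination or vaccine-era estimate from two models, one without and one with the antibiotic term, and state that the model without it is the total-effect estimate.

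For the antibiotic association:

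- add the child's earlier OM, from medical-record review or earlier study visits, where it is available;
- analyse antibiotic exposure randomized in a trial separately from prescribed exposure;
- report the coefficient as a non-causal association with likely residual confounding by indication.

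The cost is one extra model, and a smaller sample for the antibiotic association where earlier OM is not recorded. No new data collection is involved, but the usable coverage of the earlier-OM variable across studies should be checked first, because the article does not show it.

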#### Aims

To describe prevalence of nasopharyngeal pneumococcal carriage, serotype-specific carriage, and resistance over time and explore associated risk predictors.

#### Outcomes

Using all available non-interventional data, we will describe pneumococcal carriage, including serotypes and antibiotic resistance over vaccine eras (pre-PCV, PCV7, PCV10 and PCV13), reporting children positive for pneumococcus, vaccine and non-vaccine serotypes (proportions with 95% CIs) by age, region and vaccine era for comparison (chi-squared test). Regression analyses for risk predictors will use the same approach as above.

(iii) Impact of increasing valency PCVs on nasopharyngeal carriage dynamics of non-pneumococcal respiratory pathogens and antibiotic resistance over time, by region, and other known predictors (risk factors).

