Some studies included adults, some audiology testing, some virology. All available clinical, microbiological, and risk factor data for children has been included in the combined dataset. Analyses of combined data for uncommon subgroups and outcomes will be undertaken where feasible to do so. Appropriate inclusion and exclusion criteria will be applied in each analysis.

All original data were subject to quality assurance by a process of searching for missing data, logic checks, and audits against primary data sources. Data from the original studies were assessed for variables common in definition. If a comparable variable existed in multiple studies it was included in the combined dataset. Coded data were checked using the original study data dictionary to ensure coding was consistent and standardized as necessary. Variables that were not collected in multiple studies or had inconsistent definitions were not included. We aim to continue building the data asset by adding data from pre-1995 studies, and current studies after completion (bolstering data from 2015 onwards).

Over time, some children represented in this dataset have participated in more than one trial or survey (multiple enrolments). Special attention was given to the demographic data, particularly HRN (hospital registration number) to identify any child enrolled in multiple studies and across regions in the NT. This process involved looking for exact matches, (given and family name, date of birth), and highly probable matches (allowing for minor errors in spelling and dates). The HRN is a unique identifier used across the NT and is assigned to a child at birth. This was done computationally initially and finalized by manual review. A generated unique identifier enables the HRN and other identifying fields to be removed to prevent reidentification.

The data from these studies were combined to create a dataset of all study visit dates for each individual child and associated data for that visit date. Summary data of the number of individual children, enrolments, ear examinations, nasopharyngeal swabs and ear discharge swabs are presented in Table 1. The age distribution is predominantly younger children, with a median age of 2.5 years at enrolment (range 0–17.9).

**Table 1 T1:** Summary of BIGDATA participants, enrolments, ear examinations and nasopharyngeal swab data.

	**Remote Aboriginal Communities (*N*, %)**	**Urban Childcare Centers (*N*, %)**

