2003	Randomized controlled trial of surfactant vs ciprofloxacin or sofradex for resolving discharge in Indigenous children in a Tiwi community	L (1–4) RCT (1)	32 (100%) 8.3/7.9 [4.4–13.2] **years**	Ears NP ED	Spn Hi Pa
2003 PCV7	Cross sectional surveillance of OM and bacterial nasal carriage and antibiotic resistance in Indigenous children from 27 remote communities (13, 25, 33)	X Surv (27)	644 (100%) 18/18 [6-30]	NP ED	Spn Hi Mc
2003–2005	Double-blinded randomized controlled trial of azithromycin vs. amoxicillin for treatment of acute otitis media in 16 communities (25, 26, 35, 36, 40–43)	L (1-3) RCT (16)	320 (100%) 17.5/13 [6-72]	Ears NP ED	Spn Hi Mc
2003	Cross-sectional surveillance of bacterial nasal carriage and antibiotic resistance in children attending 18 urban childcare centers in Darwin and Alice Springs	X Surv (18)	303 (unknown%) 33.6/34 [2.6-66]	NP	Spn
2004	Cross-sectional surveillance of bacterial nasal carriage and antibiotic resistance in children attending 23 urban childcare centers in Darwin and Alice Springs (25)	X Surv (26)	473 (unknown%) 33.7/33.4 [3.7-83.8]	NP	Spn Hi Mc
2005	Cross sectional surveillance of OM and bacterial nasal carriage and antibiotic resistance in Indigenous children from 18 remote communities (13, 33)	X Surv (18)	819 (100%) 34/34 [0-72]	NP	Spn
2005	Cross-sectional surveillance of bacterial nasal carriage and antibiotic resistance in children attending 26 urban childcare centers in Darwin and Alice Springs	X Surv (23)	394 (11%) 35.5/36.4 [3.2-65.1]	NP	Spn
2006- 2011	PneuMum: A randomized controlled trial of pneumococcal polysaccharide vaccination for Aboriginal and Torres Strait Islander mothers to protect their babies from ear disease (44–49)	L (1-4) RCT (4)	225 (100%) birth	Ears NP ED	Spn Hi Mc Sa
2008-2013	A double blind placebo-controlled randomized clinical trial of the use of oral azithromycin in Aboriginal children between 6 months and 30 months of age presenting with asymptomatic acute otitis media without perforation	L (1-3) RCT (14)	149 (100%) 16.2/16.1 [5–30.7]	Ears NP ED	Spn Hi Mc Sa
2008–2011	High Nasopharyngeal Carriage of Non-Vaccine Serotypes in Western Australian Aboriginal People Following 10 Years of Pneumococcal Conjugate Vaccination (50)	X Surv (40)	1500 (100%) 0–101 **years**	NP ED	Spn Hi Mc Sa

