#### Outcomes

Proportions positive for carriage, proportions resistant to common antimicrobials (particularly β-lactams and macrolides), categorical carriage density and co-colonization will be reported and analyzed as per the pneumococcal/OM analyses.

(iv) Serotype specific differences in nasopharyngeal carriage between children with acute OM and diagnoses of OM with effusion or healthy ears and the impact of increasing valency PCVs on serotype dynamics and other known predictors (risk factors).

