#### Outcomes

Proportions of children (with 95%CIs) positive for pneumococci, serotype specific carriage, and vaccine and non-vaccine type carriage will be compared (chi-square) in children with and without AOM. Regression analyses will describe associations with modifiable risk factors, age and time as described above.

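### Era and AOM comparisons of carriage are assigned a chi-squared test with no adjustment, although visits repeat within children and children are grouped in communities or childcare centers

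*Protocol article*

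**What the plan says.** Under Research Questions and Hypotheses, the Outcomes text of part (ii) sets the data base ("Using all available non-interventional data, we will describe pneumococcal carriage") and the output ("reporting children positive for pneumococcus, vaccine and non-vaccine serotypes (proportions with 95% CIs"), to be shown "by age, region and vaccine era for comparison (chi-squared test". Part (iii) extends this to the other pathogens, whose results "will be reported and analyzed as per the pneumococcal/OM analyses". In part (iv), overall pneumococcal carriage, single serotypes, and "vaccine and non-vaccine type carriage will be compared (chi-square) in children with and without AOM". None of the three parts names a variant of the test, an adjustment for dependence, or a rule that reduces the data to one record per child.

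The section Data Sources, Management, and Amalgamation describes the structure of the data. The study data were "combined to create a dataset of all study visit dates for each individual child and associated data for that visit date", and "some children represented in this dataset have participated in more than one trial or survey (multiple enrolments". Table 2 gives the number of communities or childcare centers behind each study; the 2003 survey, for example, took 644 "Indigenous children from 27 remote communities".

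A correction for repeated measures appears once, in the Outcomes of part (i), and is tied to the regression analyses. The same place specifies multilevel mixed models with fixed effects for antibiotics, vaccination, age, gender and year, and with region as the only random effect. Parts (ii) and (iv) adopt that approach for risk predictors, and (iv) also for age and time. They do so in addition to the chi-squared comparisons, not in their place.

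**The concern.** The named test does not fit the data that the article describes. Several swabs from one child resemble each other, and so do children from one community. If a contrast treats them as independent, the standard error of the difference is usually too small and the test rejects a true null hypothesis more often than 5% of the time.

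The Highlights put serotype replacement across three successive vaccines at the center of the planned work, and the Introduction says that carriage data are needed to choose vaccines. Parts (ii) to (iv) spread the comparisons over several pathogens, eras, ages and regions, and (iv) adds single serotypes. An error rate above nominal in each of many comparisons makes spurious differences likely. The correction the article does plan sits in a different analysis.

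**Working it through.** **1. Inputs and Table 1.** Table 1 gives 4,692 remote and 2,358 urban children (7,050 in all), and 11,992 and 6,814 nasopharyngeal swabs (18,806 in all). Its percentages reproduce: 4,692/7,050 = 66.6% and 11,992/18,806 = 63.8%. There are 18,806/7,050 = 2.67 swabs per child over the whole asset, and 8,323/4,692 = 1.77 enrolments per remote child. No sample size, alpha or ICC is stated, so every ICC below is an assumption shown as a range.

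**2. Repeat visits left in (ii).** Limiting (ii) to non-interventional data excludes trial data, but Table 2 still lists two longitudinal cohorts: 31 children with 1 to 16 visits and 97 children with 1 to 22 visits. Mean visits per child are not given, so I put no figure on this part.

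**3. Community clustering, era contrast.** With m children per community, the design effect is DE = 1 + (m − 1) × ICC. The actual size of a nominal 5% test is 2 × [1 − Φ(1.96/√DE)]. This takes the same DE in both eras and unrelated communities. For 2003, m = 644/27 = 23.9. At ICC 0.05, DE = 1 + 22.9 × 0.05 = 2.14 and the size is 18.1%. The lowest, a middle and the highest m among the remote child surveys checked give (DE, size):

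| Survey | Children/communities | m | ICC 0.01 | ICC 0.02 | ICC 0.05 | ICC 0.10 |
|---|---|---|---|---|---|---|
| 2010 | 253/21 | 12.0 | 1.11, 6.3% | 1.22, 7.6% | 1.55, 11.6% | 2.10, 17.7% |
| 2003 | 644/27 | 23.9 | 1.23, 7.7% | 1.46, 10.4% | 2.14, 18.1% | 3.29, 28.0% |
| 2005 | 819/18 | 45.5 | 1.45, 10.3% | 1.89, 15.4% | 3.23, 27.5% | 5.45, 40.1% |

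An ordinary binomial CI for one proportion would need widening by √DE. For 2003 that is √1.23 = 1.11 to √3.29 = 1.81.

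**4. The same communities in both eras.** If communities recur and keep their level, part of the community variation cancels from the difference. Simulated size with no true era difference (20 communities of 25 children per era, 60% carriage, 8,000 runs), by correlation of community effects between eras:

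| ICC | 0 | 0.5 | 0.8 | 1 |
|---|---|---|---|---|
| 0.02 | 9.7% | 7.1% | 5.8% | 4.9% |
| 0.05 | 15.2% | 10.4% | 7.2% | 5.0% |
| 0.10 | 24.7% | 16.0% | 9.0% | 4.2% |

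The ICC here is on the logit scale, so the first column lies somewhat below the formula in step 3.

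**5. AOM contrast.** AOM status varies within communities and within children, so approximately DE = 1 + (m − 1) × ICC(AOM) × ICC(carriage).

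- Community, m = 25: both ICCs 0.05 give DE 1.06 and size 5.7% (simulated 5.5%); both 0.10 give DE 1.24 and 7.8% (simulated 8.2%).
- Child, m = 2.67: both ICCs 0.3 give DE 1.15 and 6.8% (7.3% simulated with 3 visits each); both 0.5 give DE 1.42 and 10.0% (11.7% simulated with 3 visits each).

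The value 2.67 is the average for the whole asset. The subset in (iv) may differ.

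**The case against.** The strongest reply is that the article already plans multilevel mixed models with vaccination and year as fixed effects, extends them to every part, and describes its aims as descriptive and exploratory. No alpha or decision rule hangs on a chi-squared p-value. A condensed article may also leave the variant of the test to a fuller plan: a Rao-Scott test is itself an adjusted chi-squared test, and reporting children positive could mean one record per child.

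Part of this stands. Much of the remedy is already planned, and the document does not say that replacement would be declared on these p-values alone. But the models name no child, community or center level, and they are assigned to the risk predictors while the era and AOM contrasts are given chi-squared. One record per child would remove repetition within an era but not the grouping by community. A descriptive aim does not make the test valid.

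Five stronger readings are tempting and are not supported:

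- Applying the whole-asset swabs per child (2.56 remote, 2.89 urban), or about 10 per child implied for the 2001 childcare trial, to (ii). These include trial data, and (ii) is limited to non-interventional data.
- Taking the 2005 survey as typical. It is the most clustered of the remote child surveys, and its figure assumes unrelated communities in the comparison era.
- Calling the CIs certainly too narrow. Their method is not stated.
- Calling era tables generally sparse. A serotype at 1% carriage has an expected count of 1.7 in the 174-child 2009 survey, but eras pool surveys: 253 + 568 + 276 + 371 = 1,468 children in the 2010 to 2013 remote surveys gives about 15. Sparse counts are a fair worry for the single-serotype comparisons in (iv).
- Saying that whole communities were sampled. The article says only that individually consented data are included.

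**Conclusion.** The concern holds in a limited form. As written, the era contrasts in (ii) and (iii) and the AOM contrasts in (iv) use a test whose independence assumption the data structure breaks, and the planned corrections do not reach them.

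The size cannot be fixed from the document. For era contrasts it is roughly 8% to 28% at about 24 children per community and reaches about 40% only at 45 per community with ICC 0.10. It depends on assumed ICCs and on how far communities and their effects recur between eras; with full recurrence and stable effects it is close to 5%. For AOM contrasts the excess is modest, roughly 5.5% to 12%, so a reader should not infer that (iv) rejects far too often. Any statement about narrow CIs is conditional on ordinary binomial intervals.

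**What to change.** In parts (ii), (iii) and (iv), replace the chi-squared comparisons with one of the following:

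- the mixed models already planned, with era (or AOM status in part (iv)) as the tested term, and with child and community or center levels added to region;
- GEE with robust standard errors clustered on community or center;
- Rao-Scott adjusted tests with community or center as the cluster.

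Derive the reported proportions and 95% CIs by the same method, and state whether the unit is the child or the child-visit. For sparse single-serotype comparisons in (iv), name a method that is valid for small counts.

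The cost is a change of wording, somewhat more analysis work and wider CIs. No new data are needed.
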